### Data analysis

#### Data checking and outlier analysis

Data for the baseline will be verified against manually recorded, electronically inputted records to ensure accuracy and consistency. This process involves matching data based on incident IDs when available. If incident IDs are not available, data will be matched based on deployment time.

For each phase (baseline, phase one and phase two), minimum and maximum thresholds for the primary and secondary outcomes will be established. These thresholds will be determined based on expert opinion. This approach helps in identifying potential outliers in the dataset.

#### Data analysis overview

The primary, secondary and exploratory effectiveness outcomes will be summarised in weekly periods, with separate analyses conducted for Kigali and Musanze sites. Interrupted time series models will be used independently at each site to evaluate the effect of the intervention, thereby providing intervention effects for each location. The specific interrupted time series methods used will follow best practice guidelines from a simulation comparing different statistical methods.^19^

#### What we will estimate (intervention effects to be estimated)

For Kigali, the model will evaluate both the effect of phase one and two of the 912Rwanda intervention. Estimates for the pre-intervention trend, shift changes when each of the phases of the intervention is implemented and post-intervention trends will be reported with 95% CIs. We will also estimate the combined effect of both phases of the intervention by using linear combinations of the coefficients for the shift changes and trend changes associated with each phase. Additionally, we will analyse the exploratory outcome of time from dispatch call to arrival at facility, for phase two of the intervention.

For Musanze, the model will evaluate only the modified phase two of the intervention. Estimates for the pre-intervention trend, shift change when phase two of the intervention is introduced, and the post-intervention trend will be reported with 95% CIs.

#### How we will estimate these effects

An initial Auto-Regressive Integrated Moving-Average (ARIMA) model will be fitted, including a time indicator (weekly summaries), intervention phases indicators (pre-intervention, roll-out, post-intervention) and interactions between time and intervention phases.

Diagnostic checks will be performed, and the model will be updated as needed to account for non-homogeneous variances, auto-regressive errors and non-linear trends. Regression diagnostic plots will be examined to reinforce correct transformations and error structures used.

#### Non-homogeneous variance

Homogeneity of the variance will be examined by plotting the local means of a set of consecutive observations against their SD. A clear relationship between the SD and level of the series would suggest non-homogeneous variances. This will be explored on both original and log scales, and transformations will be considered if necessary.

#### Auto-regressive errors

Autocorrelation function plots (ACF), partial ACF (PACF) and Ljung-Box tests will identify any non-random periodicity. The ACF and PACF plots will be used to determine the type and order of autocorrelation, with the PACF showing autocorrelation adjusting for intervening lags. Existing guidelines will be used to identify the autocorrelation type from these plots, for example, a significant spike at lag 1 only suggests an auto-regressive (AR1) or exponential decay structure.^20^

#### Non-linear trends

To account for any strong non-linear trend intervention effects, a polynomial spline function (eg, cubic spline) will be considered. Recommended approaches will be used to identify the appropriate number of knots. Only statistically significant non-linear terms will be included in the model. However, a cautious approach to modelling non-linear trends will be taken, as splines can be unreliable at time period endpoints, which coincide with the points of inference for interrupted time series. Additionally, including non-linear terms reduces study power and complicates interpretation as there are multiple trend coefficients instead of single pre/post-intervention coefficients.

#### Allowance for confounders

Interrupted time series analysis uses aggregate level data, limiting the possibility of adjusting for individual-level covariates. Nonetheless, the influence of confounders might be important. We will assess if there is evidence of participant’s characteristics (eg, age, sex) over the study duration. Any clear evidence of changes will be an important signal that analysis needs to be adjusted for confounders, or interpretation should account for confounding effects.

If there is evidence of confounding and minimal autocorrelation, we will use ordinary least squares (or logistic regression for binary outcomes) to allow for individual level covariate adjustment. Previous research has shown if autocorrelation is low, then this approach provides optimal effect estimates.^19^

If autocorrelation is identified, adjustment will be made using aggregate covariate measures at each time point.

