### Sample size calculation

For Kigali, which has two phases of the intervention, the sample size is based on the number of expected observations per week (ie, number of ambulance calls) of at least 50. The sample size includes 31 weeks of baseline data, 87 weeks of phase one implementation and 87 weeks of phase two implementation. We have assumed a realistic auto-regressive correlation of order 1 (exponential decay) to summarise the data’s correlation structure. A moderate effect size (standardised effect size of 0.5) is assumed, accounting for the total effect size, which is the sum of the expected level change and trend change in the two phases over the SD. This standardised effect size of 0.5 represents a target effect of half of the SD of the outcome across weekly time periods.

For example, if the average time from ambulance call to facility arrival has a mean of 70 min and SD of 30 (across 108 weeks), this would be equivalent to a total intervention effect of 15 min. A total sample size of 108 observations (weekly means of duration from ambulance deployment to hospital), with an equal number of observations across the three periods, would provide more than 80% power across nearly all auto-regressive correlations (autocorrelation <0.7) at 5% significance. This is a conservative estimate as we have over 87 weekly observations in each post-roll-out period for both phases of the intervention.

For Musanze, which has only one phase of the intervention, we use a similar approach but adjust for the simpler design. The sample size includes 104 weeks of baseline data and 48 weeks of phase two implementation. Assuming the sample weekly rate of ambulance calls, same auto-regressive correlation structure and a moderate effect size (standardised effect size of 0.5), which is the sum of the expected level and trend change in the one phase intervention over the SD, a total sample size of 72 observations would provide more than 80% power across all auto-regressive correlations values of less than 0.6.

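### The individual-level fallback for confounding is justified by low between-week autocorrelation alone, which does not protect its standard errors against correlation among trips in the same week

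*Protocol article*

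**What the plan says.** Under Data analysis overview, the week is the unit of analysis: "The primary, secondary and exploratory effectiveness outcomes will be summarised in weekly periods". An ARIMA model is then fitted to those summaries.

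Allowance for confounders adds two branches for covariate adjustment. The first is entered on two conditions, "If there is evidence of confounding and minimal autocorrelation", and there "we will use ordinary least squares (or logistic regression for binary outcomes) to allow for individual level covariate adjustment". The reason given is "Previous research has shown if autocorrelation is low, then this approach provides optimal effect estimates". The second branch applies when autocorrelation is found. It stays with weekly data and adjusts for covariates aggregated at each time point.

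The dependence checks are those under Auto-regressive errors: "Autocorrelation function plots (ACF), partial ACF (PACF) and Ljung-Box tests will identify any non-random periodicity". The protocol names no check of correlation within a week. For the individual-level branch it names no week effect and no clustered variance.

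The Sample size calculation for Kigali gives the weekly volume, "expected observations per week (ie, number of ambulance calls) of at least 50", and the length of the series, "31 weeks of baseline data, 87 weeks of phase one implementation and 87 weeks of phase two implementation".

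**The concern.** Autocorrelation describes how one week resembles the next. Trip-level regression also needs residual independence among trips within the same week. Rain, road closures, staffing gaps, fuel shortages or network outages can lengthen most trips in one week and be unrelated to what happens the week after. Such shocks leave the ACF flat and still make that week's trips alike.

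This matters because of where the intervention information lies. Every trip in a week has the same values of the level and trend terms, so those coefficients are estimated from the number of weeks. Trip-level OLS or logistic regression with model-based standard errors credits them with the number of trips. The coefficients affected are those the protocol will report with 95% confidence intervals. A move to the adjusted analysis could therefore shorten the intervals for a reason unrelated to the covariates, and the two adjustment branches would give intervals of unequal validity.

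The stated support speaks of effect estimates. Even if that holds for the point estimates, it does not establish the standard errors of a trip-level model.

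**Working it through.** The plan gives no coverage or type I error figure for this branch, so there is none to reproduce. Its power claim of more than 80% concerns weekly means, and this point does not rest on it.

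**Inputs**
- Trips per week, m = 50 (Sample size calculation, stated as a minimum).
- Kigali weeks: 31 + 87 + 87 = 205 (same section).
- Two-sided 5% test, critical value 1.96 (assumed two-sided; the protocol says 5%).
- Within-week ICC: not in the protocol; a range from 0 to 0.10 is assumed.
- Model-based standard errors, equal trip numbers per week, and weekly shocks independent between weeks (assumed).

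**Formulae.** For terms constant within a week:
- design effect DE = 1 + (m − 1) × ICC
- ratio of reported to correct standard error = 1/√DE
- type I error = 2 × [1 − Φ(1.96/√DE)]

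Worked case, ICC 0.02: DE = 1 + 49 × 0.02 = 1.98; 1/√1.98 = 0.711; type I error = 2 × [1 − Φ(1.393)] = 16.4%.

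| Assumed ICC | DE | SE ratio | Coverage of 95% CI | Type I error |
|---|---|---|---|---|
| 0 | 1.00 | 1.00 | 95.0% | 5.0% |
| 0.005 | 1.245 | 0.90 | 92.1% | 7.9% |
| 0.01 | 1.49 | 0.82 | 89.2% | 10.8% |
| 0.02 | 1.98 | 0.71 | 83.6% | 16.4% |
| 0.05 | 3.45 | 0.54 | 70.9% | 29.1% |
| 0.10 | 5.90 | 0.41 | 58.0% | 42.0% |

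**Simulation check.** 205 weeks of 50 trips, segmented model with two level and two trend changes, 2,000 runs per ICC:
- Trip-level OLS covered the level-change terms 95–96% of the time at ICC 0, 89–90% at 0.01, 84% at 0.02, 71–73% at 0.05 and 58–61% at 0.10.
- OLS on weekly means covered about 95–96% at every ICC.
- Trip-level OLS with week-clustered standard errors covered about 93–96%, with the phase-one level change (which rests on the 31 baseline weeks) at the low end.
- The Ljung-Box test (10 lags, residuals of the weekly model) rejected in 8–9% of runs at every ICC, including 0. That is above its nominal 5%, but it does not rise with the ICC, so the test does not see shocks of this kind.

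**Clinical outcomes.** These come from registries at the referral hospitals. In the 2021/2022 Kigali figures under Study setting, one referral hospital took 13% of patients. With half going to three named hospitals and over 30% to health centres or managed on site, under 20% remained for other hospitals. If those shares hold, 50 trips give between 0.13 × 50 = 6.5 and about 0.33 × 50 = 16.5 registry patients per week:
- m = 6.5: DE = 1.055 and 1.11 at ICC 0.01 and 0.02; type I error 5.6% and 6.3%.
- m = 16.5: DE = 1.155 and 1.31; type I error 6.8% and 8.7%.

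**The case against.** The strongest reply is that the protocol names an estimator and not its variance. OLS or logistic regression with week-clustered standard errors would satisfy the text, and an analysis plan that is not shown could say so. The protocol also promises regression diagnostics on the error structure. This limits the point to model-based standard errors. It does not remove it: the protocol gives a reason for leaving the weekly analysis, and that reason concerns dependence between weeks only.

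A second reply is that real shocks may last more than a week and would then show up in the ACF. Suppose the shocks had lag-1 correlation 0.5 (assumed). The lag-1 correlation of weekly means would be 0.5 × ICC/[ICC + (1 − ICC)/50], or about 0.17, 0.25 and 0.36 at ICC 0.01, 0.02 and 0.05, against a band of 1.96/√205 ≈ ±0.14. The checks would then often send the analysis to the aggregate branch. That stands for persistent shocks, but not for shocks confined to a week.

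Three stronger readings are tempting and are not supported:
- A reader might infer that every covariate-adjusted analysis is inflated. Only the individual-level branch is exposed, and only if the residual ICC exceeds zero. Covariates that explain the shocks would lower it.
- A reader might carry the 50-per-week figures over to mortality, length of stay or intensive care. Registry patients per week are probably far fewer.
- A reader might take the sample-size example, with an SD of 30 min across weeks, to mean that nearly all variance lies between weeks. That needs a trip-level SD near 30 min, which the protocol does not give. With ICC = (30²/SD² − 0.02)/0.98, an assumed trip SD of 60 or 100 min gives about 0.23 or 0.07. The 30 min is also hypothetical and may contain trend and intervention steps. Fully independent trips would need a trip SD of 30 × √50 ≈ 212 min around a mean of 70, so the example sits awkwardly with an ICC of zero, but it does not fix a value.

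**Conclusion.** The point holds for the conditional individual-level branch. Low between-week autocorrelation is not a sufficient condition for trip-level regression with model-based standard errors, and the planned ACF, PACF and Ljung-Box checks do not detect week-specific shocks that are independent from week to week.

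For the time outcomes at 50 trips per week, standard errors would be understated by about 18%, 29% and 46% at assumed ICCs of 0.01, 0.02 and 0.05. At a fixed ICC, more trips per week would make this worse. For the registry-based outcomes the effect is likely to be modest. The direction is certain if weeks share shocks; the size depends on an ICC the protocol does not give. The branch could still determine the adjusted primary result, so it should be corrected before that analysis is run.

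**What to change.** Keep the individual-level covariate adjustment and state how within-week correlation will be handled, by one of these:
- week-clustered standard errors with a small-sample correction, needed because the Kigali baseline has only 31 weeks and uncorrected clustering ran slightly low for the phase-one level change;
- a random week effect in the trip-level model;
- a two-stage analysis that adjusts trips for covariates and fits the segmented model to the adjusted weekly means.

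Apply the same rule to the logistic models. Low autocorrelation should no longer serve as the only justification for the branch.

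The cost is a sentence or two of text and minor code, with no new data. Intervals become wider: by factors of √1.49 = 1.22, √1.98 = 1.41 and √3.45 = 1.86 at ICCs of 0.01, 0.02 and 0.05, and hardly at all if the ICC is near zero.

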#### Missing data

Missing data may occur for covariate or outcome data. When using aggregate covariate data, we will explore the robustness of various approaches, using simulation-based methods to account for missing data, as standard multiple imputation methods are not amenable. Missing outcome data will be addressed similarly. If individual level data are used, we will use standard multiple imputation methods to handle missing data.

### Objective 2: implementation of intervention

#### Outcomes

The protocol is designed to examine not only the direct effects of the intervention but also implementation outcomes, in terms of sustainability, quality of delivery and potential for broader application. Data collection, analysis and integration for implementation outcomes will be guided by the RE-AIM QuEST framework,^21^ which includes quantitative assessments of implementation outcomes, with qualitative assessments to explore the reasons behind quantitative findings.

The mixed-methods approach allows a comprehensive assessment of the intervention’s implementation across five dimensions: Reach, Effectiveness, Adoption, Implementation and Maintenance. Specific outcomes for each of the RE-AIM QuEST framework dimensions are described in table 2, including the sources of quantitative and/or qualitative data for each outcome.

**Table 2 T2:** RE-AIM-QuEST framework applied to 912Rwanda evaluation

Domain	Description	Quantitative measures	Qualitative measures
**Reach**	Engagement with target population, including coverage and representativeness	The use of the intervention including: Crew phone usage (number of crews taking out phones each shift/number of shifts) Phones in use (number) Log-in rate (actual average number of users logged in each day over expected average number) Call volume (calls per day, including location, caller type, condition)	Focus group discussions with dispatch, ambulance crew and facility staff will explore: Reasons for using or not using the 912Rwanda, with attention to influences of organisational context which might support or constrain use How well the intervention reaches target populations Representativeness of target populations
**Effectiveness**	Impact on key outcomes (health, behavioural) and any unintended consequences	Effectiveness outcomes are described in table 1	Focus group discussions with dispatch, ambulance crew and facility staff will explore: Whether users think the intervention is effective and their reasons for thinking whether it is effective or not User perspectives on unintended consequences (positive and negative)
**Adoption**	Extent to which organisations or settings are willing to adopt the intervention	Adoption will be captured as the ‘Criteria for Success’ that would lead to the intervention being rolled out throughout Rwanda. This will be determined through consensus at MCDA workshops (online supplemental file 2). The proportion and representativeness of settings/staff that adopt the intervention.	In-depth interviews with policy makers from MDCA workshops about: The willingness of involved institutions and stakeholders to implement the intervention Whether institutions agree to deliver the intervention and the extent to which they wish to integrate it into existing practices Organisational readiness (including, eg, staffing, infrastructure, resource and/or governance challenges) Factors that could influence adoption such as organisational culture, leadership support and resource availability
**Implementation**	Fidelity, consistency and adaptations in delivery	Implementation will be assessed using data from surveys on Acceptability, Feasibility and Appropriateness.^23^ Fidelity will be assessed using: Proportion of patient journeys where all data for an interface have been completed by users Proportion of patient journeys where any data have been completed for an interface (interfaces include ambulance, dispatch and facilities) Number of times there were user-related hardware failure, user-related software failure, inappropriate use of hardware, internet failure or lack of mobile data Acceptability will be summarised by Number of DDSA decisions overridden by staff (ambulance crew, facility and dispatch) AIM survey Appropriateness will be summarised using IAM survey	In-depth interviews or focus group discussions with dispatch, ambulance crew and facility staff to understand the barriers and facilitators to successful implementation of the intervention regarding: Fidelity to the intervention protocol Quality of delivery of the intervention Acceptability of the intervention Appropriateness of the intervention Reasons given by dispatch for overriding the DDSA Reasons for not fully using the intervention Additionally, a list of adaptions of the intervention will be captured when they are made; these will be summarised, including detail of adaption made, date and reason.
**Maintenance**	Extent to which effects are sustained over time at individual/organisational levels.	Maintenance will be assessed as the continued use of the system, measured by quantitatively drawing on implementation Fidelity outcomes in each interface, 1 year after study end. The proportion and representatives of settings/staff that continue to deliver the intervention of time.	In-depth interviews with policy makers to capture sustainability beyond the duration of the project and possibility of abandonment of intervention, including to which extent the intervention has been integrated into routine practice and continues to be used over time and to explore factors influencing maintenance such as ongoing support, funding and changes in the environment.
**QuEST**			
**Domain**	Description		**Methods**
**Quality**	Consistency and standards of delivery, particularly in terms of delivery and participant experience		In-depth interviews or focus group discussions with dispatch, ambulance crew, facility staff and/or policy makers
**Effectiveness (QuEST**)	Effectiveness re-evaluated with emphasis on real-world conditions, assessing outcomes in varied contexts		
**Scalability**	Potential to expand across larger populations or different settings		
**Transferability**	Adaptability to fit different cultural, organisational or resource contexts		

* Stakeholders include practitioners/health workers/technical implementers/civil servants; decision makers; Ministry of Health officials; political actors; Civil Society Organisations /Non-Governmental Organisations/Principal Investigators/Chief Investgators.

AIM, Acceptability of Intervention Measure; DDSA, destination decision support algorithm; MCDA, Multiple-Criteria Decision Analysis; QuEST, Qualitative Evaluation for Systematic Translation; RE-AIM, Reach, Effectiveness, Adoption, Implementation, Maintenance.

Maintenance will be assessed using quantitative fidelity outcomes collected from 912Rwanda platform in month 12 after the study end. Further funding will be applied to assess this outcome.

In addition, to specifically assess intent to adopt, a Multi-Criteria Decision Analysis (MCDA) workshop will be held to understand additional outcomes which are not captured in the above-described study outcomes which are important to policy makers. Data to inform these additional outcomes will be collected by the study team, as feasible.

#### Data collection

Quantitative implementation data will be collected from 912Rwanda databases and validated surveys conducted with different user groups (ambulance, dispatch and facility staff).

Qualitative data will be collected through focus group discussions with user groups and policy makers. Structured interview and focus group discussion topic guides will be developed based on findings from the quantitative RE-AIM findings and the experiences of the study team during implementation of the intervention. Tailored topic guides will be created to elicit the specific perspectives of each participant group (service users, providers and decision makers).

